##### 11.3.4.3 Bleeding accident

Bleeding accidents including upper gastrointestinal, cerebral, peripheral bleeding during CRRT is observed and documented.

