| Adverse event check                           |           | X                      | X                    |                        |
| Residual renal function check     |           |                        |                      | X                      |
| Mortality check                               |           |                        | X                    | X                      |
| Blood loss                                    |           | X                      | X                    |                        |
| Packed RBC transfusion                        |           | X                      | X                    |                        |
| Free frozen plasma, Platelet      |           | X                      |                      |                        |

1: administered until treatment is concluded

2: If patients are improved, closing examination was performed at discontinuation of CRRT. However, if the patient has deceased, the last examination before death was used.

3: Body temperature, pulse rate, respiratory rate, blood pressure was examined before other examination was performed. During CRRT, vital sign was examined every 4 hours. At screening, body temperature was examined rectally.

4: Pregnancy test was performed in female without sterilization or any effective contraception in child-bearing age.

5: Detailed examination was as following;

- Hematologic: Hemoglobin, Hematocrit, RBC, WBC, Platelet, differential count, ESR

- Biochemical: Alkaline phosphatase, BUN, Creatinine, SGPT (ALT), SGOT (AST), Total bilirubin, Uric acid, Na, K, Cl, Ca, P, CRP, total CO2
  - Arterial Blood Gas: O2, CO2, arterial pH, HCO3, Base excess/deficit, Oxygen saturation
  - Lipid: Cholesterol
  - Urine analysis: pH, Protein, Glucose, Ketone, WBC, RBC
  - Coagulation test: aPTT, PT-INR
  - Specific coagulation test: fibrinogen, fibrin degradation product
- During CRRT, Clinicopathologic examination was performed every 72 hours. If CRRT was discontinued before 72 hours, examination was performed at discontinuation. Uine analysis was performed at screening and closing. Specific coagulation examination was substituted for the examination performed recently
- 6: Subject compatibility assessment was performed based on all examination, personal history and inclusion/exclusion criteria. Patients who were fit in these criteria was enrolled as subjects.

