| Adverse event check                           |           | X                      | X                    |                        |
| Residual renal function check     |           |                        |                      | X                      |
| Mortality check                               |           |                        | X                    | X                      |
| Blood loss                                    |           | X                      | X                    |                        |
| Packed RBC transfusion                        |           | X                      | X                    |                        |
| Free frozen plasma, Platelet      |           | X                      |                      |                        |

1: administered until treatment is concluded

2: If patients are improved, closing examination was performed at discontinuation of CRRT. However, if the patient has deceased, the last examination before death was used.

3: Body temperature, pulse rate, respiratory rate, blood pressure was examined before other examination was performed. During CRRT, vital sign was examined every 4 hours. At screening, body temperature was examined rectally.

4: Pregnancy test was performed in female without sterilization or any effective contraception in child-bearing age.

5: Detailed examination was as following;

- Hematologic: Hemoglobin, Hematocrit, RBC, WBC, Platelet, differential count, ESR
- Biochemical: Alkaline phosphatase, BUN, Creatinine, SGPT (ALT), SGOT (AST), Total bilirubin, Uric acid, Na, K, Cl, Ca, P, CRP, total CO2
- Arterial Blood Gas: O2, CO2, arterial pH, HCO3, Base excess/deficit, Oxygen saturation
- Lipid: Cholesterol
- Urine analysis: pH, Protein, Glucose, Ketone, WBC, RBC
- Coagulation test: aPTT, PT-INR
- Specific coagulation test: fibrinogen, fibrin degradation product

During CRRT, Clinicopathologic examination was performed every 72 hours. If CRRT was discontinued before 72 hours, examination was performed at discontinuation. Uine analysis was performed at screening and closing. Specific coagulation examination was substituted for the examination performed recently

6: Subject compatibility assessment was performed based on all examination, personal history and inclusion/exclusion criteria. Patients who were fit in these criteria was enrolled as subjects.

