#### 8.2.13 Checking adverse events

Patients are repeatedly educated to report any information of adverse events, and researchers are obligated to investigate adverse events by interview and physical examination. When investigating adverse events, date of manifestation, disappearance, severity, actions that took step related to the study medication, relation with the study medication, any medication that is suspected to have relations with the adverse events except the study medication and treatment related to adverse event was sought.

The typical symptoms that are classified as adverse events are described as follows.

(1) Fever

Fever is checked by documenting body temperature, its severity is investigated, and finally the relationship between the medication and symptom is evaluated.

(2) Subjective and objective symptom

Subjective and objective symptom is investigated through the researcher's examination, its severity is investigated, and finally the relationship between the medication and symptom is evaluated.

(3) Clinicopathologic examination

Any abnormality of clinicopathologic examination is followed until it is recovered, and the predicted cause is evaluated.

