#### 8.3.2 Medication phase (randomization and after initiation of CRRT)

- ① After screening, change in medication history is checked.
- ② Every examination including clinicopathologic test and assessment is collected to finally evaluate the patient's suitability as a subject.
- ③ Patient is given a randomization number by random enrollment.
- ④ Study medication is administered.
- ⑤ Hematologic examination was conducted every 72 hours after initiation of CRRT.
- ⑥ Vital sign (blood pressure, body temperature, pulse rate, respiratory rate) is assessed every 4 hours after initiation of CRRT.
- ⑦ Filter life span and reason for discontinuation is sought.
- ⑧ Blood loss is checked at filter change after initiation of CRRT.
- ⑨ Transfusion (packed RBC, free frozen plasma, platelet concentrate) is assessed after initiation of CRRT.
- ⑩ Any changes in medication are recorded.
- ⑪ Adverse event is investigated.
- ⑫ Bleeding accident is checked.

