### 8.3.4 Follow-up

Follow-up investigation includes recovery of renal function, patients' mortality. When patient's condition is improved and CRRT is not necessary, patient is followed whether he or she is on dialysis at discharge, and renal recovery is sought at 1st outpatient department visit after discharge. Also, mortality at discharge and 28 days after initiation of CRRT is investigated. Follow-up investigation is conducted according to patient's outpatient department visit schedule and no extra-visit for the study is planned.

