#### 11.3.4 Safety data

##### 11.3.4.1 Adverse event

All adverse events that have been reported during the study will be charted, and incidence of adverse event will be calculated.

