#### 13.3 Criteria for patient's treatment after clinical study

Subject who dropped out or unresponsive to the study medication is supervised to be treated with other appropriate management, and due to possibility of delayed adverse event, patient is always allowed to access medical assistance under researcher's supervision.

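### Scheduled adverse event and bleeding collection ends with CRRT, whose length is itself a compared outcome, and new non-fatal events from then to day 28 have no planned collection

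*Protocol*

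**What the plan says.** The schedule tables in the protocol summary and in 8.1 are alike. The row "Adverse event check" is marked under Treatment and Closing, and the Follow-up cell is empty. The note on Closing says that in improved patients the "closing examination was performed at discontinuation of CRRT"; for patients who die, the last examination before death is used.

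Bleeding appears in the visit lists only in 8.3.2, the medication phase ("Bleeding accident is checked"). It is not listed in 8.3.3 (completion or discontinuation) or 8.3.4 (follow-up). Section 11.3.4.3 describes the record: "Bleeding accidents including upper gastrointestinal, cerebral, peripheral bleeding during CRRT is observed and documented".

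After CRRT, 8.3.4 states: "Follow-up investigation includes recovery of renal function", together with mortality at discharge and at 28 days after CRRT initiation. No extra study visit is planned.

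The general safety text is wider. Section 11.3.4.1 charts all adverse events reported in the course of the study, sets no stop date, and says that the "incidence of adverse event will be calculated". No exposure time is attached to that incidence.

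**The concern.** The scheduled safety window is as long as each patient's CRRT. Section 7.1 says that this length varies with the patient's condition, and 11.1.2 and 11.2.2 make it a secondary endpoint compared between arms. Early death also shortens it, and ICU mortality is the primary endpoint. A plain incidence over such a window mixes the daily risk of an event with the number of days watched. At the same daily risk, the arm with longer CRRT records more patients with events, and the arm that stops or dies earlier records fewer.

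The second consequence is a gap in the data. A new non-fatal bleed after CRRT stops but before day 28 falls outside 11.3.4.3 and has no scheduled check. No cause of death is requested, so a fatal late bleed would count as a death but not as a bleed.

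Both matter because bleeding is the central safety question. Section 6.1 enrols patients for their bleeding tendency, 3.1.2 names safety as a purpose, and the precautions in 9.1 warn that the drug can worsen haemorrhage when used in an extracorporeal circuit.

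**Working it through.** **The texts side by side**

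| Item | Runs until | Where |
|---|---|---|
| Adverse event check | Closing: end of CRRT, or last examination before death | Schedule tables and their note 2 |
| Bleeding accidents | End of CRRT | 8.3.2, 11.3.4.3 |
| Mortality | Discharge, and 28 days after CRRT initiation | 8.2.15, 8.3.4 |
| Adverse events in the analysis text | No stop date | 11.3.4.1 |
| Events or abnormal laboratory values already open | Resolution or recovery | 8.2.13, 12.5.1 |

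The real tension is between the schedule cells, with 11.3.4.3, and the open-ended wording of 11.3.4.1.

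**Effect of window length**

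The protocol gives no bleeding rate and no CRRT duration, so there is no figure of its own to reproduce and every input here is assumed. Take the same daily bleeding risk *q* in both arms, ignore death, and let CRRT last *d* days. The chance of a recorded bleed is 1 − (1 − *q*)^*d*. With *q* = 3%:

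- 5 days: 1 − 0.97^5 = 14.1%
- 8 days: 1 − 0.97^8 = 21.6%
- Difference: 7.5 points, with no true difference in daily risk

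Over a wider range, using a constant hazard *h* per day and 1 − exp(−*h* × *d*):

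| CRRT days, arm 1 vs arm 2 | *h* = 0.01 | *h* = 0.03 | *h* = 0.05 | Apparent risk ratio |
|---|---|---|---|---|
| 3 vs 3 | 3.0% vs 3.0% | 8.6% vs 8.6% | 13.9% vs 13.9% | 1.0 |
| 3 vs 5 | 3.0% vs 4.9% | 8.6% vs 13.9% | 13.9% vs 22.1% | 1.59 to 1.65 |
| 4 vs 7 | 3.9% vs 6.8% | 11.3% vs 18.9% | 18.1% vs 29.5% | 1.63 to 1.72 |
| 3 vs 9 | 3.0% vs 8.6% | 8.6% vs 23.7% | 13.9% vs 36.2% | 2.60 to 2.91 |

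**What a rate per CRRT-day does**

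In the 3% example, the expected days at risk up to a first bleed are (1 − 0.97^*d*) / 0.03, which is 4.71 days for *d* = 5 and 7.21 days for *d* = 8. The rates are 0.141 / 4.71 = 0.030 and 0.216 / 7.21 = 0.030 per day. The false gap disappears, provided the daily risk is constant.

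**Size of the unscheduled period**

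If CRRT lasts 3 to 9 days, then 1 − 3/28 = 89% to 1 − 9/28 = 68% of a 28-day window has no scheduled bleeding or adverse event check in a patient who survives.

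**Scale against the trial**

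With 33 patients per arm (6.3.1), 7.5 points is 0.075 × 33 = 2.5 patients. The standard error of the difference is √(0.141 × 0.859/33 + 0.216 × 0.784/33) = 9.4 points.

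**The case against.** Recording bleeding while the circuit and drug are running is a recognisable on-treatment choice. Section 3.2 supports it by citing a short half-life and an effect confined to the circuit. That justifies a short tail for drug effect. It does not justify comparing arms over windows of possibly different length, and the control arm receives no drug whose half-life could set its window.

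The illustration is wholly assumed. Nothing in the protocol shows or predicts different CRRT durations, and with equal durations the artefact is nil. Even the example gap is smaller than one standard error, and the safety sections prescribe no between-arm test. All of this stands, and it limits the claim to a possible bias of unknown size and direction.

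A reader might infer that serious events before day 28 are simply not collected. The documents do not support that. Deaths, which 12.1 counts as serious, are captured to day 28, and 11.3.4.1, 12.1 and 12.5.1 set no stop date. Section 8.3.3 asks for an adverse event investigation at study completion without naming the end of CRRT, although the schedule note ties Closing to it. Late non-fatal adverse events are therefore unscheduled rather than excluded; only bleeding is expressly limited to CRRT. In an open-label trial, though, unscheduled reporting may be uneven between arms.

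A reader might also see contradictions elsewhere, but these passages can stand beside the schedule. Section 8.2.13 ("Any abnormality of clinicopathologic examination is followed until it is recovered") and the reporting until resolution in 12.5.1 concern events already open. Section 13.3 ("due to possibility of delayed adverse event, patient is always allowed to access medical assistance") concerns access to care, not data collection.

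An SAP could settle how rates are presented. It could not recover post-CRRT bleeds that were never collected.

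**Conclusion.** The point holds in a limited form. Scheduled adverse event checks and the bleeding record end with CRRT or death. CRRT length is a post-randomisation quantity that the protocol itself compares between arms, so the plain incidence may differ between arms through window length alone. New non-fatal bleeds and serious adverse events from then to day 28 have no planned collection.

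The size is unknown. It is zero if CRRT durations are alike, and the apparent risk ratio is about 1.6 to 2.9 under the unequal durations assumed above. Those figures rest on a constant and equal daily risk, assumed durations, and no allowance for death. It would go too far to say that the safety comparison is biased; the supportable statement is that it may be. This is a worthwhile and cheap improvement, not a flaw that invalidates the trial.

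**What to change.** - In 8.1 (and the matching summary table), 8.3.4 and 11.3.4, collect bleeding accidents and serious adverse events in both arms over one fixed window, from randomisation to 28 days after CRRT initiation. This is the time point already used for mortality in 8.2.15 and 8.3.4. Section 7.1 counts its 28 days from CRRT discontinuation and should be aligned so that the window has one end point.
- Do not end the window at ICU discharge. ICU stay is also a secondary endpoint (11.1.2), so that window could differ between arms for the same reason.
- Handle death as a competing event, since it ends observation for bleeding and is expected in about half the patients (6.3.2).
- Mark the adverse event check under Follow-up.
- Present events during CRRT also as a rate per CRRT-day by arm. The data for this are already collected.
- Reconcile the schedule tables and 11.3.4.3 with the open-ended wording of 11.3.4.1.

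The cost is a wording and table amendment, some chart abstraction after CRRT stops, and a question at the existing day-28 status check. Capture of non-fatal events after hospital discharge will be less complete, and the report should say so. No visit or test is added.

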## 12. Safety evaluation method including adverse event, evaluation criteria and reporting method

### 12.1 Definition of safety related terms

#### (1) Adverse events (AE)

Adverse event is a sign, symptom, or disease which occurs after attending the clinical study and is neither intentional nor desirable. Adverse event does not necessarily have to have cause-and-effect relationship with the study medication.

#### (2) Adverse drug reaction (ADR)

“Adverse drug reaction” is a reaction that has reasonable doubt that the medication and the reaction that has cause-and-effect relationship, or at least the possibility is not ruled out.

#### (3) Serious and Unexpected Adverse Drug Reaction

“Serious and Unexpected Adverse Drug Reaction” is the nature and severity of reaction that is not anticipated according to available medication related information and if this happens, spontaneous report should be followed.

#### (4) Serious AE/ADR

Serious AE/ADR is adverse event or adverse drug reaction that has occurred in any dosage of medication during the clinical study, and is as follows;

- ① Patient's death during the study
- ② Life threatening circumstances (when the patient is exposed to the risk of death by the incidence of reaction)
- ③ When persistent or significant disability or functional deterioration is anticipated.
- ④ When the patient is need to hospitalized or prolong hospitalization period in already hospitalized patient
- ⑤ When causes congenital disability or abnormality
- ⑥ Other medically significant circumstances

Even if it is not listed above, when patient's safety or health is thought to be compromised, under supervision of attending physician and related specialist's opinion, the reaction is considered as serious adverse event and appropriate management is followed accordingly.

## 12.2 Evaluation method

- Adverse event is newly developed symptom that was not observed before study enrollment, and is not intended symptom and sign that is transient related to the usage of the study medication, regardless of cause-and-effect relationship with the study medication.
- The undesirable clinical sign and symptom that was observed during or before screening is documented in physical examination data sheet, and is not documented as adverse events.
- The adverse event is thoroughly reported in the adverse event data sheet (symptom and sign, observation date, duration), and event that is not documented in the data sheet is considered as subjective symptom.
- The severity of adverse event is referred to evaluation criteria by the researcher and the severity is graded.
- The cause-and-effect relationship between the symptom and medication is referred to evaluation criteria and graded in 6 phases.

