## 6. Inclusion/exclusion criteria, target number of subjects and its estimation basis

### 6.1 Inclusion criteria

Patients are selected as subjects with following conditions;

- (1) Adult male/female patients aged from 18 to 80.
- (2) ICU patients who are hemodynamically unstable to be in need of CRRT and has one of the hemorrhagic tendencies described as follows.
  - ① Platelet < 100,000
  - ② aPTT > 60 sec
  - ③ PT-INR > 2.0
  - ④ Active bleeding
  - ⑤ Major surgery within 48 hours
  - ⑥ History of cerebral hemorrhage or major bleeding within 3 months
  - ⑦ Septic shock or DIC
- (3) Patients or his/her legal guardian has voluntarily agreed to participate in the study and provided written informed consent.

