#### 8.2.4 Physical examination

Physical examination is performed at screening and considered as baseline data, afterwards the final physical examination is performed at cessation of CRRT by identical researcher. Physical examination contains allergic, cardiovascular, pulmonary, gastrointestinal, hepatic, endocrinologic, renal, genitalial, musculoskeletal, skin, connective tissue, neurologic psychological and other examination.

Notable disturbance during physical examination at screening is recorded in physical examination section of data sheet. After initiation of CRRT, notable disturbance that can be identified as adverse event should be noted in the adverse event section of data sheet. However, if the abnormal physical examination was redundant as screening, it should be recorded in physical examination.

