## 12.5 Reporting method

### 12.5.1 Reporting the adverse event

- Principal investigator should inform the researcher, patients or legal guardian of possible adverse events and education the researchers to document all events that occur after administration of study medication.
- The systemic or clinicopathologic signs after administration of study medication is documented and stored to data sheets according to clinical study management regulation including the characteristics, event time, severity, management, treatment medication, duration, cause and effect relationship between the study medication.
- Principal investigator should describe and evaluate all sign/symptoms during clinical study when reporting study result. When serious adverse drug reaction occurs during the clinical study, principal investigator should report to IRB and decide continuance or discontinuation of the study. When prompt report is necessary due to following incidence, the funder should promptly report to the incidence to Korean food and drugs administration.
- “Serious adverse drug reaction” is a sign that cannot be excluded as a result of study medication administration and include following conditions.
  - ① Patient’s death during the study
  - ② When the patient’s life is threatened
  - ③ When lasting or significant disability or functional deterioration occurs
  - ④ When the patient needs hospitalization or delay in discharge when already hospitalized.
  - ⑤ When the medication causes congenital deformity or abnormality
  - ⑥ Other medically significant circumstances
- Additional safety information should be periodically reported until the adverse event is resolved (when the adverse event is resolved or impossible to follow up).
- Principal investigator should follow declaration of Helsinki regarding all matters.

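### The adverse event rules exclude signs present at screening with no provision for worsening, and give conflicting starts of recording, one of which the control arm never reaches

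*Protocol*

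**What the plan says.** **What counts as an adverse event.** Section 12.1(1) is broad: "Adverse event is a sign, symptom, or disease which occurs after attending the clinical study". Section 12.2 is narrower: "Adverse event is newly developed symptom that was not observed before study enrollment". Its next item adds that an undesirable sign or symptom "observed during or before screening is documented in physical examination data sheet, and is not documented as adverse events". Nothing in section 12 readmits a condition that gets worse.

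Section 8.2.4 treats existing findings differently: "After initiation of CRRT, notable disturbance that can be identified as adverse event should be noted in the adverse event section of data sheet". The exception is an abnormality that merely repeats what was found at screening, which stays in the physical examination record.

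**Who enters.** One of the qualifying bleeding tendencies in section 6.1 is "Active bleeding".

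**When recording starts.** Section 12.5.1 has the principal investigator train researchers to "document all events that occur after administration of study medication". It repeats that starting point in the next item: "The systemic or clinicopathologic signs after administration of study medication is documented".

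**How safety is analysed.** The safety set in 11.3.1 includes the no-anticoagulation group. Section 11.3.4.1 computes incidence from the reported adverse events. Section 11.3.4.3 has bleeding accidents during CRRT noted as a separate item, and 8.3.2 lists the bleeding check separately from the adverse event check.

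**The concern.** More bleeding is the obvious harm to look for when an anticoagulant is compared with none in patients selected for bleeding risk. The general precautions in section 9.1 say that use in the extracorporeal circuit can worsen bleeding. The background (3.2) also describes earlier evidence in terms of bleeding that increased, decreased or did not change. The expected harm is thus partly a change in a condition that is already present, and the definition in 12.2 leaves that kind of event out.

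Two things are at stake. The first is completeness: if 12.2 is followed as written, a patient who enters with a bleed that then worsens adds nothing to the incidence in 11.3.4.1 for that worsening. A serious event under 12.1(4) must first be an adverse event or adverse drug reaction, so the omission can carry over into serious-event reporting. The second is comparability. The trial is open label (4.3), and where sections disagree on when recording begins, staff who know the allocation will settle the matter case by case.

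Both are rules for collecting data. An event that was never recorded cannot be recovered by an analysis plan.

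**Working it through.** The protocol attaches no figure to this point, so the check sets the passages side by side.

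**Step 1. A bleed ongoing at screening that worsens during CRRT.**

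| Section | Is the worsening an adverse event? |
|---|---|
| 12.1(1) | It can be read as one; the definition has no new-onset condition |
| 12.2 | No; the sign was present at screening |
| 8.2.4 | By implication yes; only an unchanged finding is held back |
| 11.3.4.3 | Not stated; it may be noted as a bleeding accident |

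Section 8.2.4 does not repair 12.2. It contradicts it, and it concerns physical examination, which the protocol schedules only at screening and at the end of CRRT.

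**Step 2. Do the other records guarantee that the worsening is counted?**

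- Bleeding accidents (8.3.2, 11.3.4.3) apply to both arms and have no new-onset condition. They also have no definition, no grading, no rule for worsening, and no stated link to the incidence in 11.3.4.1 or to reporting under 12.5.
- Severe hemorrhage (10.1) is a drop-out criterion, and the reason for stopping is recorded. No text says that it is also entered as an adverse event.
- Transfusion amounts (8.2.17, 11.3.3.2) and laboratory values compared with screening (11.3.4.2) may reflect a worsening bleed, but they do not classify it as an event.

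Some of the information is therefore likely to exist somewhere in the record. Its entry into the adverse event count is not assured.

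**Step 3. A past bleed that has resolved.** Section 6.1 also admits patients with a major bleed in the previous 3 months. A fresh bleed in such a patient can count as newly developed, so the problem is clearest for bleeding still ongoing at entry.

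**Step 4. Start of recording.**

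| Section | Start | Treated arm reaches it | Control arm reaches it |
|---|---|---|---|
| 12.1(1) | Joining the study | Yes | Yes |
| 12.2 | Enrolment | Yes | Yes |
| 8.2.4 | CRRT initiation | Yes | Yes |
| 8.3.2 | Phase covering randomisation and the time after CRRT initiation | Yes | Yes |
| 12.5.1 (twice) | After study medication | Yes | No |

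An event between randomisation and the start of CRRT counts under 12.1 and 12.2 in both arms and does not count under 8.2.4. Under 12.5.1 it does not count in the treated arm unless medication has already been given, and the wording gives no answer in the control arm.

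**The case against.** The strongest reply is that bleeding is followed closely whatever 12.2 says. It has its own check in both arms, separate from the adverse event item, and its own safety section. Severe hemorrhage is a recorded reason for stopping, transfusion is summarised, and 8.2.4 leaves room to record a changed finding. This stands against any inference that worsening is simply missed. It does not show that worsening reaches the adverse event count, because no text makes that link.

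A reader might also infer that the control arm has no start of recording. The protocol does not support that: 12.1, 12.2, 8.2.4 and 8.3.2 all give starts that control patients reach, and the schedule in 8.1 does not restrict the adverse event check by arm. The fault is that the starts conflict.

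A reader might further infer that a worsened baseline bleed can never be reported as serious. Section 12.1(4) lists death and life-threatening circumstances without a new-onset test, and ends with a general clause for cases where safety or health is thought to be compromised. So a route exists, at the investigator's discretion.

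Finally, the drug is used to prime the circuit (7.2.2) and is given throughout CRRT (7.2.3, 8.2.10). The first dose should therefore fall close to CRRT initiation, and the practical difference in windows may be small. That is fair. The baseline-sign rule also applies equally to both arms. Neither the size nor the direction of any bias can be shown from the protocol.

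**Conclusion.** The point holds in a limited form. Section 12.2 excludes signs present at screening, has no rule for worsening, and conflicts with 8.2.4, in a trial that admits patients because they are bleeding and tests a drug the protocol says can make bleeding worse. Worsening of a bleed ongoing at entry is not assured of entering the incidence in 11.3.4.1 or serious-event reporting. Separately, the start of recording differs between sections, and 12.5.1 uses one that the control arm never reaches.

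This is a wrongly fixed rule, not detail left for later. It affects the safety comparison. It does not touch the primary endpoint or the sample size.

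The effect cannot be put into numbers. The protocol gives neither the share of patients bleeding at entry nor the interval from randomisation to CRRT. Multiplying an assumed share by the 33 patients per group would count patients exposed to the rule, not events lost. The conclusion assumes that staff follow 12.2 as written; if they follow 8.2.4, less is lost, but the protocol does not say which prevails.

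**What to change.** 1. **Section 12.2:** state that any increase in the severity, frequency or seriousness of a condition present at screening is an adverse event, and that new or worsened bleeding accidents are also entered as adverse events. Reword the exclusion so that it covers unchanged findings only, in line with 8.2.4.
2. **Section 12.5.1:** in both places, replace the start tied to study medication with one start common to both arms, for example randomisation.
3. **Sections 8.2.4, 8.3.2, 12.1 and 12.2:** reconcile the start of recording to that same point.

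The cost is a few sentences and an instruction on the case report form. No treatment, dose or clinical rule changes. The downside is more events to record and a higher reported adverse event rate, because many critically ill patients will have baseline conditions that worsen.
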